#### 7.3.2 Analysis of Secondary Efficacy Variables

- Time-weighted Sum of Pain Intensity Differences at rest at 6 h, 12 h, 18 h, and 12-24 h (SPID6, SPID12, SPID18, SPID12-24);

The mean, standard deviation, maximum, minimum and median will be calculated, and sequential tests between groups will be performed, the same as the primary efficacy variable.

- Time-weighted Total Pain Relief at 6 h, 12 h, 18 h, 24 h, and 12-24 h (TOTPAR6, TOTPAR12, TOTPAR18, TOTPAR24, TOTPAR12-24);

Calculation formula:  $TOTPAR_t = \sum [PRT * (TIME_t - TIME_{t-1})](h)$ .

The mean, standard deviation, maximum, minimum and median will be calculated, and sequential tests between groups will be performed, the same as the primary efficacy variable.

➤ Time to the first use of rescue analgesics (h)

Sequential tests will be performed between the groups, and the comparison of differences between the groups will be performed using the log-rank test. For subjects who do not use rescue analgesics, the data will be treated as censored data with censoring time of 24 h.

➤ Cumulative amount of rescue analgesics from 0 h to 24 h

The mean, standard deviation, maximum, minimum and median will be calculated, and sequential tests between groups will be performed, the same as the primary efficacy variable.

➤ Number of treatments of rescue analgesia from 0 h to 24 h

The mean, standard deviation, maximum, minimum and median will be calculated, sequential tests between groups will be performed, and Wilcoxon rank sum test will be used.

➤ Total number of presses and number of effective presses of PCA pump from 0 h to 24 h

The mean, standard deviation, maximum, minimum and median will be calculated, sequential tests between groups will be performed, and Wilcoxon rank sum test will be used.

➤ Percentage of subjects who do not use rescue analgesics from 0 h to 24 h

The proportion of subjects who do not use rescue analgesics and its 95% CI will be calculated in each group. The 95% CI will be calculated by Clopper-Pearson method. Sequential tests will be performed between the groups and the rate difference between the two groups and its 95% CI will be calculated.

➤ The subject's satisfaction score with analgesic treatment

The mean, standard deviation, maximum, minimum and median will be calculated, sequential tests between groups will be performed, and Wilcoxon rank sum test will be

used.

- The investigator's satisfaction score with analgesic treatment

The mean, standard deviation, maximum, minimum and median will be calculated, sequential tests between groups will be performed, and Wilcoxon rank sum test will be used.

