**Withdrawal by the Subject**

1. Subjects may withdraw from the study at any time.
2. The investigator may decide to discontinue the investigational product and/or withdraw the subject from the study if any medical condition occurs prior to dosing or during the administration, which may put the subject at risk, or if the subject is unable to complete the study as specified in the protocol.

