### **Data Analysis/Statistical Method**

#### **Sample Size**

With reference to the results of the foreign study TRV130-3002, assuming that the primary efficacy variable SPID24 in the SHR8554 0.75 mg group in this study is comparable to the efficacy in the 0.35 mg group in the TRV130-3002 study, and conservatively assuming that the mean (standard deviation) of SPID24 in the low dose group of this study is 88 (45), and the mean (standard deviation) of SPID24 in the placebo group is 70 (40), it's estimated to need 118 subjects in each group by the sample size calculation formula (PASS) of comparing the means of two samples to achieve the power of 90% with  $\alpha = 0.05$  (two-sided), provided that the four groups are designed in a 1:1:1:1 ratio. Considering the dropout rate of 10%, each group is planned to enroll 132 subjects, with a total of 528 subjects.

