### **Efficacy Analysis**

- 1) Time-weighted Sum of Pain Intensity Differences at rest at 6 h, 12 h, 18 h, 12h-24 h, and 24 h (SPID6, SPID12, SPID18, SPID12-24 and SPID24) will be compared between groups using analysis of variance;
- 2) Time-weighted Total Pain Relief at 6 h, 12 h, 18 h, 24 h, and 12-24 h (TOTPAR6, TOTPAR12, TOTPAR18, TOTPAR24, and TOTPAR12-24) will be compared between groups using analysis of variance;
- 3) The time to the first use of rescue analgesics will be compared between groups by nonparametric test;
- 4) Cumulative amount of rescue analgesics from 0 h to 24 h will be compared between groups using analysis of variance;
- 5) The number of treatments of rescue analgesia from 0 h to 24 h, the total number of presses and number of effective presses of PCA pump from 0 h to 24 h will be compared between groups by nonparametric test;
- 6) The percentage of subjects who do not use rescue analgesics from 0 h to 24 h will be compared between groups using chi-square test or Fisher's exact probability method;
- 7) The subject's satisfaction score with analgesic treatment will be compared between groups by nonparametric test;
- 8) The investigator's satisfaction score with analgesic treatment will be compared between groups by nonparametric test.

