### 6.1 Full Analysis Set (FAS)

It includes all subjects who received at least one dose of study drug after randomization in accordance with the intent-to-treat (ITT) principle.

Description of baseline demographic data and efficacy evaluation will be performed in the FAS.

Treatment groups will be based on randomization.

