### 7.1.3 Estimation of Missing Values

For the pain intensity (PI) score, if the subject does not have the PI score during night sleep, NRS = 3 will be uniformly used for imputation;

For the pain relief (PR) score, if the subject does not have the PR score during night sleep, the previous PR score will be uniformly used for imputation.

Regarding the scores after rescue analgesia, within 6 h after rescue analgesia with parecoxib sodium and within 2 h after rescue analgesia with sufentanil, PI/PR scores at pre-specified time points will be imputed using the PI/PR scores before rescue analgesia.

In other cases, missing PI and PR scores will be imputed using the last observation carried forward (LOCF) method.

Missing values in other secondary efficacy variables and safety evaluations will not be estimated.

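### Censoring every unrescued subject at 24 h counts unobserved time after early withdrawal as rescue-free, which tilts the time-to-first-rescue log-rank test toward the arm that loses more subjects

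*Combined protocol and SAP*

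**What the plan says.** SAP 7.3.2 tests time to first rescue sequentially, high dose then low dose against placebo, and "the comparison of differences between the groups will be performed using the log-rank test". Its only censoring rule is: "For subjects who do not use rescue analgesics, the data will be treated as censored data with censoring time of 24 h". The protocol (Efficacy Analysis) says only that "The time to the first use of rescue analgesics will be compared between groups by nonparametric test", and gives no censoring rule.

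Early exit is foreseen. The protocol's section on withdrawal states that "Subjects may withdraw from the study at any time", and the investigator may also withdraw a subject during dosing. If a subject withdraws consent to further disclosure or contact, data collection stops. The full analysis set nevertheless keeps "all subjects who received at least one dose of study drug after randomization" (SAP 6.1). The Sample Size section plans for losses: "Considering the dropout rate of 10%, each group is planned to enroll 132 subjects".

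Nothing else in the SAP settles the case. Section 7.1.3 says "Missing values in other secondary efficacy variables and safety evaluations will not be estimated", which sits awkwardly with assigning 24 h of follow-up to someone seen for 2 h. The sensitivity analyses in 7.5 concern SPID24 only. For the related endpoint, 7.3.2 says "The proportion of subjects who do not use rescue analgesics and its 95% CI will be calculated in each group", without saying how an unrescued early leaver is classed.

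**The concern.** Right-censoring should mark the point at which knowledge of a subject's status stops. Under the rule as written, a subject who leaves early without rescue sits in the denominator of every later risk set and can never contribute an event. The apparent rescue rate in that arm is diluted, increasingly so as the subjects still observed are rescued and the leavers form a larger share of those nominally at risk.

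Equal dilution in both arms largely cancels. Unequal dilution makes the arm that loses more subjects look better at avoiding rescue. This endpoint receives formal two-sided 0.05 tests, so a difference in retention could be read as an analgesic effect, or could hide one.

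**Working it through.** **The plan's own figure.** The documents give no calculation for the log-rank endpoint. The primary sample size supplies the group size and reproduces:

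- Average variance: (45² + 40²)/2 = 1812.5
- n = 2 × (1.960 + 1.282)² × 1812.5 / 18² = 117.6, so 118 per group
- 118/0.90 = 131.1, so 132 per group and 528 in total

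**Inputs.** From the documents: 132 per arm; two-sided 0.05; 10% overall dropout; phase 2 (201P) rescue-free rates of 40% on placebo and 60% on 0.75 mg, from 10 subjects each. Assumed: the split of withdrawal between arms, its timing, exponential rescue times (a front-loaded Weibull with shape 0.5 was also tried), and withdrawal unrelated to pain.

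**Hand check of the mechanism.** Take no treatment difference, 60% rescued by 24 h, and withdrawal of 15% on one arm and 5% on the other, all at the start.

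- If S is the share of observed subjects not yet rescued, the apparent hazard is the true hazard times (1−d)S / [d + (1−d)S].
- At S = 0.7, halfway between 1 and 0.4, the factors are 0.595/0.745 = 0.799 and 0.665/0.715 = 0.930. The apparent hazard ratio is 0.859, with log −0.152, where the truth is 1.
- Events: 132 × 0.6 × (0.85 + 0.95) ≈ 143. The shift in the test statistic is about 0.152 × √143 / 2 ≈ 0.91.
- Rejection probability: P(Z > 1.96 − 0.91) + P(Z < −1.96 − 0.91) ≈ 15%.

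Leaving somewhat after the start should give a little less.

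**Simulated type I error** for one comparison with placebo (6,000 trials per setting, Monte Carlo error about 0.3 points at 5%). Ranges run over 40% and 60% rescued and, except in the 8/12 row, front-loaded rescue.

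| Withdrawal, placebo / active | As written, leaving spread over 0–24 h | As written, leaving in first 4 h | Censored at leaving |
|---|---|---|---|
| 10% / 10% | 4.6–5.4% | 4.9–5.1% | 4.8–5.3% |
| 8% / 12% | 4.8–5.4% | 5.0–6.8% | 4.4–5.3% |
| 5% / 15% | 5.7–6.8% | 8.3–12.3% | 4.6–5.4% |
| 0% / 20% | 7.1–11.3% | 19.9–36.3% | 4.4–5.2% |

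All four rows average 10% over the two arms, the planned overall rate. With 40% rescue-free and leaving at 0.5 to 4 h, separate runs of 15% versus 5% gave 12.3% to 14%, hence about 13%. With 60% rescue-free the figure was 8.3%. In the settings with clear inflation, nearly all the excess favours the arm with more withdrawal.

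**Simulated power** with 60% rescued on placebo and 40% on active (4,000 trials per setting):

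| Withdrawal, placebo / active | As written | Censored at leaving |
|---|---|---|
| 10% / 10% | 87–89% | 89–90% |
| 5% / 15% | 95–96% | 88–91% |
| 15% / 5% | 66–83% | 90–91% |

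The apparent gain in the second row is bias.

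**Rescue-free percentage.** Suppose the true rates are 60% and 40%, with 15% and 5% leaving very early.

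- Leavers counted as rescue-free: 0.85 × 60 + 15 = 66% against 0.95 × 40 + 5 = 43%, a 23-point difference.
- Leavers counted as not rescue-free: 51% against 38%, a 13-point difference.
- The truth is 20 points, so neither coding recovers it.
- If both arms are truly 60% rescue-free, the second coding compares 51% with 57%: standard error 0.0612, z = 0.98, about 16.5% false positives. The first compares 66% with 62%: standard error 0.0590, z = 0.68, about 10%.

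**The case against.** **No inflation is shown.** With equal withdrawal, the test keeps its level. A modest imbalance, or withdrawal spread over the day, moves it little. The documents give no split by arm or time. Some of the 10% may never be dosed and so fall outside the full analysis set. This stands. A reader might infer that the log-rank test simply loses its error rate, but the documents support only a conditional risk.

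**The direction is unknown.** A reader might also infer that the opioid arms would lose more subjects and so be favoured. The protocol's 201P summary gives no support: one adverse event led to withdrawal among 51 subjects, on morphine, which is only described in this trial. Vomiting was listed at 40% on both placebo and 0.75 mg. Placebo subjects may also leave for lack of efficacy, and the rule would then work against the drug. This stands too.

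**Leaving treatment is not leaving observation.** The protocol separates stopping the product from withdrawing from the study, asks for every effort to complete assessments at withdrawal, and records concomitant medication throughout the study. For a subject who stops the pump but remains observed, censoring at 24 h is correct. This narrows the problem to subjects whose data collection ends before 24 h. It does not remove it, because the SAP gives those subjects no other censoring time.

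**Other rescue endpoints.** Counting early leavers as failures in the rescue-free percentage defines a different estimand and, as shown above, can be further from the truth. It does not belong in the main analysis.

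**Conclusion.** The concern holds in a limited form. Applied as written, SAP 7.3.2 treats unobserved time as rescue-free time and biases the time-to-first-rescue comparison toward the arm with more early withdrawal. The size depends on a withdrawal pattern that the documents do not give: about 13% two-sided error at 15% versus 5% with leaving at 0.5 to 4 h and 40% rescue-free, about 7% if spread over 24 h, and about 5% if equal. Power can fall to 66–83% if placebo is the arm losing 15%. These figures assume that withdrawal is unrelated to pain.

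The endpoint is secondary and SPID24 is untouched, so this should be fixed but does not threaten the trial's main conclusion.

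**What to change.** In SAP 7.3.2, censor subjects without rescue at the earlier of 24 h and the last time their rescue status was observed. State that subjects who stop the pump but remain under observation keep 24 h.

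Add a sensitivity analysis that counts withdrawal for lack of efficacy as an event, because censoring at withdrawal assumes that leaving is unrelated to the need for rescue.

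For the rescue-free percentage, state how unrescued early leavers are classed. As sensitivity analysis only, report the 24 h Kaplan-Meier estimate under the new censoring rule or the result with early leavers counted as not rescue-free.

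The cost is a few sentences and one derived variable, the time of last observed rescue status. Sample size, the primary analysis and the choice of tests do not change.

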## 7.4 Safety Evaluation

### 7.4.1 Drug Exposure

The subject's drug exposure in each group will be described as mean, standard deviation, maximum, minimum and median.

### 7.4.2 Adverse Events

TEAEs will be coded according to the current version of MedDRA at the time of coding and processed in the statistical analysis.

- The number and incidence of treatment-emergent adverse events/treatment-related adverse events, treatment-emergent serious adverse events/treatment-related serious adverse events, and adverse events leading to withdrawal from the study/treatment-related adverse events will be summarized by SOC and PT;
- Treatment-emergent adverse events/treatment-related adverse events occurring in  $\geq 10\%$ / $\geq 5\%$  of subjects ( $\geq 10\%$ / $\geq 5\%$  in any group) will be summarized by PT;
- The number and incidence of adverse events of special interest, i.e., nausea, vomiting, dizziness, respiratory depression (respiratory depression defined as respiratory rate  $< 8$  beats/min and/or oxygen saturation  $< 90\%$ ) during the treatment period, will be summarized;

If a subject experiences multiple AEs, he/she will be counted only once in incidence calculation; if a subject experiences the same AE for multiple times, he/she will be counted only once in the incidence calculation of this AE.

AEs will be summarized in frequency tables by system organ class (SOC) and preferred term (PT). Incidence (number of subjects: number of subjects with at least one AE) will

be calculated by system and symptom/sign.

The number and incidence will be calculated by severity and relationship to study drug, SOC and PT, respectively (for AEs with repeated occurrences, the event with the worst severity will be calculated for analysis).

A listing of all AEs and SAEs experienced by the subjects will be provided.

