### **Safety Analysis**

Safety analysis will be tabulated and analyzed by descriptive statistics based on the Safety Set (SS), including AEs, laboratory tests, vital signs, electrocardiogram data, etc.

AEs will be coded according to MedDRA. AEs will be summarized by treatment group. The incidences of AEs, drug-related ADRs, SAEs, etc. will be summarized by system organ class (SOC) and preferred term (PT), and relevant adverse events will be tabulated. Incidences (number of subjects: number of subjects with at least one AE) will be calculated by SOC and PT; if a subject experiences the same AE for many times, the AE with the highest severity will be counted.

Other safety variables will be summarized using descriptive statistics. The mean, standard deviation, maximum, minimum and median will be used to describe each measurement and change from baseline. The frequency and percentage will be used to describe categorical

variables.

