#### 4.2 Treatment-related Adverse Events

The investigator should comprehensively assess and judge the relationship between the AE and the investigational product according to the five-level classification of "related, possibly related, unlikely related, unrelated, not determined". "Related", "possibly related" and "not determined" adverse events are listed as treatment-related adverse events (TRAEs), the sum of which will be the numerator to calculate the incidence of TRAEs, while the number of all subjects for safety evaluation is the denominator.

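### SAP 7.4.2 attaches the worst-severity rule for repeated adverse events to the by-relationship table as well, so that table can disagree with the TRAE incidence

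*Combined protocol and SAP*

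**What the plan says.** SAP 7.4.2 (Adverse Events) defines the two breakdowns in one sentence: "The number and incidence will be calculated by severity and relationship to study drug, SOC and PT, respectively". The bracket that closes the sentence is the only selection rule given for repeated events: "for AEs with repeated occurrences, the event with the worst severity will be calculated for analysis".

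The same section also has a separate bullet for overall incidence by SOC and PT, which covers "The number and incidence of treatment-emergent adverse events/treatment-related adverse events, treatment-emergent serious adverse events/treatment-related serious adverse events". Its counting rule makes no reference to severity: "if a subject experiences the same AE for multiple times, he/she will be counted only once in the incidence calculation of this AE". A listing of every AE and SAE is also planned.

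SAP 4.2 uses a five-level causality scale, "related, possibly related, unlikely related, unrelated, not determined". It classes related, possibly related and not-determined events as TRAEs, "the sum of which will be the numerator to calculate the incidence of TRAEs".

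The protocol's Safety Analysis text (section 10.5) names the incidences of AEs, drug-related ADRs and SAEs by SOC and PT, and defines incidence as the number of subjects with at least one AE. It then adds: "if a subject experiences the same AE for many times, the AE with the highest severity will be counted".

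Neither document says which relationship to report when episodes of the same event were judged differently, or what to do when two episodes have the same severity.

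**The concern.** A subject with several episodes of one event has to be reduced to one row per table. For a severity table, the usual choice is the worst severity. For a relationship table, the matching choice is the strongest relationship. Choosing the episode by severity and then reading off its relationship answers a different question, and it can hide a milder episode that the investigator attributed to the drug.

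Safety is part of the stated objective, and nausea, vomiting and dizziness are singled out for separate description. These symptoms can recur in one subject over 24 hours of patient-controlled dosing. If the relationship table and the TRAE table give different numbers of subjects with, say, related vomiting, a reader of the report cannot tell which is right, and the programmer will have had to choose without guidance.

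**Working it through.** The plan states no figure that depends on this rule, so there is nothing to reproduce. The check has three steps.

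**1. The rule applied to example records.** Take four subjects with nausea:

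- Subject 1: one moderate episode, unrelated; one mild episode, related.
- Subject 2: one mild episode, related.
- Subject 3: one moderate episode, related; one mild episode, unrelated.
- Subject 4: one mild episode, unrelated.

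Subjects with at least one related episode: 1, 2 and 3, so three. Taking the worst-severity episode first and then reading its relationship gives subjects 2 and 3, so two. Subject 1 is lost from the related rows. Subject 3 is not, because there the worst episode is the related one. If both of subject 1's episodes had been mild, the rule would select neither, and the row would depend on the sort order of the data.

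A loss therefore needs three things together: the same term recorded more than once in the subject, different causality judgments, and a worst (or tie-selected) episode that is unlikely related or unrelated.

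**2. Share misfiled among subjects with two episodes, at least one of them related.** Inputs from the protocol's account of study 201P: 63 drug-related AEs against 217 TEAEs, so p = 63/217 = 0.29, and all AEs mild or moderate. Assumption: each episode is moderate with probability s = 0.2 to 0.3, independently of relationship.

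With independent causality judgments, the share with discordant episodes is 2p(1−p) / [1−(1−p)²] = 2(0.29)(0.71) / (1−0.71²) = 0.4118/0.4959 = 0.83.

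Among discordant pairs, the unrelated episode is strictly worse with probability s(1−s) = 0.16 to 0.21. The share misfiled is then:

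- ties resolved to the related episode: 0.83 × 0.16 to 0.83 × 0.21 = 13 to 17%;
- ties resolved at random: 0.83 × 0.5 = about 42%;
- ties resolved to the unrelated episode: 0.83 × 0.79 to 0.83 × 0.84 = 66 to 70%.

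Independence drives these figures, and two episodes of one symptom in one subject are likely to be judged alike. With within-subject correlation r, the discordant share becomes 2p(1−p)(1−r) / [1−(1−p)²−r·p(1−p)]. At an assumed r = 0.8 this is 0.0824/0.3312 = 0.25. The misfiled share falls to 0.25 × 0.16 to 0.25 × 0.21 = about 4 to 5% with ties to related, and about 12% with random ties.

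The value 0.29 also pools all terms and all arms of 201P, placebo and morphine included. It is not specific to nausea or vomiting.

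**3. Subjects per group.** Loss = n × incidence × share with repeats × share whose worst episode is unrelated while a milder one is related. With n = 132 (planned per group) and 40% incidence (nausea, and also vomiting, in the 0.75 mg group of 201P), the base is 132 × 0.40 = 52.8 subjects. Both shares are assumed:

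- repeats 10%, discordant 5%: 52.8 × 0.10 × 0.05 = 0.3 subjects (0.2 percentage points);
- repeats 30%, discordant 20%: 52.8 × 0.30 × 0.20 = 3.2 subjects (2.4 points);
- repeats 50%, discordant 50%: 52.8 × 0.50 × 0.50 = 13.2 subjects (10 points).

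The range is wide because the documents fix neither share.

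**The case against.** Three objections carry weight.

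First, the sentence in 7.4.2 ends its list of breakdowns with the word respectively, so the bracket may have been meant for severity only. That is a fair reading. But the relationship table then has no rule at all for repeated events with discordant causality, and a sentence is still needed.

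Second, a reader might infer that drug-relatedness in this trial is undercounted in general. The documents do not support that. The TRAE definition in SAP 4.2 has no severity filter, the TRAE summaries in 7.4.2 have their own bullet and count each subject once, and every event is listed. Subject 1 in the example stays in the TRAE incidence. The events of special interest are summarised regardless of relationship.

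Third, a reader might infer from the protocol's Safety Analysis text that ADR incidence itself loses subjects, which would reach the between-group ADR comparison planned in the synopsis. That happens only if events are reduced to the most severe one before the filter on relationship. Neither document states that order, and it fits poorly with the protocol's own definition of incidence as subjects with at least one event. It remains an open point of wording and is not a demonstrated error.

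Nor do the documents support a claim that the distortion is larger in some arms. They give no repeat frequency by arm and no pattern of attribution over time.

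**Conclusion.** The point holds as a defect in one descriptive table. Followed literally, SAP 7.4.2 can file a subject as not related in the by-relationship table when the same subject has a TRAE under SAP 4.2, and it leaves severity ties undefined. With 201P showing only mild and moderate events, ties may be common.

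The size is unknown. The percentages above apply only to subjects with repeated episodes of a term and depend on assumptions about severity, ties and correlation of causality judgments. The per-group counts depend on two shares that the documents do not give. Subjects with a single episode of a term are unaffected, and so are the primary analysis, the type I error control and the sample size. This is a minor correction, worth making because the text as written gives the wrong selection for that table.

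**What to change.** In SAP 7.4.2, replace the bracket with text along these lines:

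*For repeated occurrences of the same PT (or within the same SOC) in a subject, the severity table counts the occurrence with the worst severity. The relationship table counts the occurrence with the strongest relationship, in the order related, possibly related, not determined, unlikely related, unrelated. TRAE/ADR incidence counts each subject with at least one related, possibly related or not-determined occurrence, whatever its severity. Events are filtered on relationship before any selection by severity.*

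The last two sentences also settle the order of steps that the protocol leaves open. They replace the sum of events in SAP 4.2 as a numerator over subjects, which does not fit the once-per-subject rule in 7.4.2.

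The cost is a short SAP wording change and one sort key in the table program, with no new data. The number of subjects shown as related in that table may rise slightly.
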